#### Quality of life

2.6.10

The Expanded Prostate Cancer Index Composite Short Form will be used to capture prostate cancer symptomology, specifically around urinary and bowel function, and sexual health (52). This is a valid and reliable tool for capturing health-related quality of life for those with prostate cancer (53). Further, the Functional Assessment of Cancer Therapy—General will also be used to measure four domains of health-related quality of life including physical, social, emotional and functional wellbeing (54).

#### Cardiorespiratory fitness

2.6.11

Aerobic fitness will be assessed using the Åstrand Rhyming submaximal exercise test on a recumbent cycle ergometer (Lode, The Netherlands). This protocol is described in detail elsewhere (55), but briefly, this single-stage test commences at 50 watts of resistance, with periodic increases in resistance if heart rate is below 120 beats per minute (56, 57). Throughout the 6-min assessment, the participant is required to maintain a pedal rate of 50 revolutions per minute (56). Heart rate obtained during minute 5 and 6 of the test are averaged together to use in the nomogram and equation to predict VO_2_max (57).

Given the population of interest, and the likelihood of existing factors that influence heart rate including cardiovascular comorbidities and various medications, participants in this study may not be able to achieve the desired heart rate, but their RPE on the 6 to 20 Borg scale should reflect a submaximal intensity between 11 and 13.

#### Blood biomarkers

2.7.12

Neurofilament light chains will be measured in plasma samples collected pre- and post- intervention. Neurofilament light chains are a novel biomarker highly specific to neural damage, thought to relate to neurocognitive decline (58). Participants will be able to attend one of several pathology laboratories around the ACT region in the week prior to commencing, and week after completing, the training intervention/wait-list control period.

#### Anthropometric measures

2.7.13

Pre- and post- intervention, bodyweight will be obtained digitally using a Wedderburn TANITA scale to the nearest 0.1 kg, with participants being asked to take off shoes and remove heavy clothing. Height will also be obtained using a SECA model to the nearest centimeter. These measures will be used to calculate body mass index (kilograms of weight/ height in meters squared). Waist/hip circumference will be measured using an anthropometric tape measure in accordance with World Health Organization guidelines (59). These measures will be used to calculate waist to hip ratio to provide an indication of cardiovascular health in this population. Manual blood pressure will be also obtained using a Littmann Classic stethoscope and Prestige Medical cuff by trained research staff, pre- and post- the 8-week intervention period.

### Statistical analysis

2.7

Quantitative analyses will be conducted in the R statistical package. Analyses will follow an intention-to-treat principle, whereby all randomized participants will be included in the groups to which they were allocated, regardless of adherence or withdrawal. The mean and standard deviation of the outcome measures pre-, mid-, and post-intervention will be calculated for each group. Group differences in baseline characteristics will be assessed with one-way ANOVA or Kruskal-Wallis test (pending normality of data). Data related to the feasibility of the intervention (e.g., adherence and adverse advents) will be reported as frequencies. To estimate intervention effects (i.e., cognitive and fatigue outcomes), Linear Mixed Models with a random intercept fitted for subjects will be implemented using the lme4 package (60), to consider the repeated measures nature of the data and interindividual variability. These models inherently accommodate incomplete outcome data under a missing-at-random assumption. As per previous work (22), hypothesis testing from pilot studies should be interpreted with caution, as the small sample sizes can result in imprecise estimates and are unlikely to reach statistical significance. Effect sizes will be calculated for the pairwise changes in primary outcome measures between the experimental conditions. Effect sizes will be calculated as Cohen’s d using the pooled standard deviation of the random effects to account for a Linear Mixed Model structure. Effect sizes will be interpreted as small, moderate, and large based on cut-off points of 0.2, 0.5 and 0.8, respectively.

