### Randomization, group allocation, and blinding

2.3

All participants who give consent and fulfill the inclusion criteria will be stratified by age (+/− 65 years) and then randomly allocated in a 1:1:1:1 ratio to one of four treatment arms: (1) physical training, (2) cognitive training, (3) concurrent cognitive and physical training, or, (4) wait-list control. Randomization will use a computer-generated sequence of numbers in blocks of variable sizes in a 1:1:1:1 ratio by a researcher not directly involved in the study. Allocation concealment will be ensured using sequentially numbered, opaque, sealed envelopes prepared by this independent researcher and kept inaccessible to recruitment and assessment staff until completion of baseline testing. After baseline testing (outlined below), this envelope with the group allocation will be delivered to the participant and training staff. Once opened, the training staff will provide information to the participant about the allocated intervention arm. Blinding of intervention allocation is not possible for any participant or the training staff. Team members completing the post-intervention assessments will be blinded to participant group allocation and will not be involved in data analysis. Treating clinicians involved in referring potential participants to the study (including author GP) will be blinded to whether potential participants choose to engage with the study.

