#### Cognitive function

2.6.7

The benefit likelihood on cognitive function will be assessed pre- and post-intervention in a single sitting, with participants located individually in a quiet room with minimal distractions. Potential harm will be defined as negative effect sizes consistently across most cognitive outcomes, clearly favoring the control group. Participants will be seated with a laptop and mouse at an individual desk and will be instructed to perform the tasks as quickly and accurately as possible. All tasks were downloaded on 6th April 2022 from the Millisecond (Seattle, USA) test library using the Inquisit Player version 6.5.2 and will be delivered in English (42). Some modifications to the base scripts will be made to be more suitable for this population including changes in timings, trial number, and colloquial understandings. Each assessment will include a series of practice trials to be completed before test trials. The cognitive battery takes ~50 min to complete and consists of five tasks in the cognitive domains that have been reported to potentially be impacted by ADT including visuospatial skills, spatial memory, and executive functioning (10). Such domains may also be responsive to concurrent training (28). Category Switch will be the first assessment and will assess executive function through a divided attention task (43). This will be followed by the Visual Simon task assessing executive function, working memory and inhibition (44). The next assessment will be the Groton Maze test assessing immediate and short-term visuospatial memory (45). The second last assessment will be the Visual Search task (Divided Attention) which is a divided attention task assessing visuospatial skills and spatial memory (46). Lastly, the Psychomotor Vigilance test assesses attention, response speed and motor co-ordination (47).

Visuospatial awareness (and fine motor skills) will also be assessed with the Purdue Pegboard. It involves the participant placing as many small pegs as possible into a pegboard in 30 s, with both their dominant hand, non-dominant hand, as well as both hands simultaneously. This assessment has specifically been included as visuomotor slowing has been shown in those with advanced prostate cancer (McGinty et al., 2014; Salminen et al., 2004) and may be sensitive to physical activity.

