#### Fatigue

2.6.9

Fatigue is commonly reported in men with prostate cancer and represents a response, and potential side-effect of the intervention. As such, it will be assessed though several means. As an overall intervention outcome, fatigue will be evaluated using the Short-Form 12 (49), including the vitality subscale questions, which will capture subjective general fatigue, pre-intervention, mid-intervention (end of Week 4) and post-intervention.

The NASA Task Load Index will also be employed for participants in all intervention groups for both sessions in Week 1 and Week 8 to provide insight into the perceived mental workload experienced by the participants. The individual dimensions of the NASA Task Load Index will be analysed separately, as research recommends (50). Rate of Perceived Exertion (RPE) will be captured during each of the physical or concurrent training sessions as a measure of perceived physiological fatigue (51).

Further, we anticipate that fatigue in response to the training intervention itself (any arm) will be common, thus the following measure specifically articulates how participants are coping with the intervention. This will be captured before every intervention session (irrespective of intervention arm) using the graded scale according to the Common Terminology Criteria for Adverse Events (40) as categorized below, and reported as a secondary outcome rather than an adverse event:

Grade 1: Fatigue relieved by rest.Grade 2: Fatigue not relieved by rest; limiting instrumental activities of daily living.Grade 3: Fatigue not relieved by rest; limiting self-care activities of daily living.

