### Data security and storage

2.8

Two separate databases, a research database and a participant database will be utilized in this study to maintain participant confidentiality. The research database will comprise of de-identified demographic information for analysis and all recorded outcome measures (including questionnaires), assessment scores, and training data. No other personal information shall be stored in the research database. Each participant will be assigned unique ID code by an individual independent of the research team that is classified based on age stratification 65 years and younger or >66 years. This participant code will be used to collate all data pertaining to that individual. When conducting data collection, this code will be used within the lab, and data will be stored alongside their participant code in the research database.

The participant database will store the participants’ personal and contact information necessary for safety and contact purposes, as well as the participant code. This will ensure identifiable personal data is not stored with research data. The participant database will be stored in a password protected file and will serve as the key between identifiable information and de-identified code for the study. Only the Chief Investigator (BR) and lead logistics team members will have access to this file.

All members of the listed research team will have access to the research database unless otherwise specified, and data on this server will not be permitted to be shared beyond the research team without appropriate consent. If any additional researchers wish to be granted access to the research database, they will need to be approved on the ethics application prior to access. All team members will be asked to acknowledge in writing before accessing any participant data that they will comply with the National Health and Medical Research Council guidelines in Human Research.

The research database will be stored on secure, password protected University of Canberra (UC OneDrive) servers with access outlined above. All data will be stored for a minimum of 15 years in line with data storage for clinical trials. The use of the research data will be in line with the terms and conditions of the funding body. Any sensitive personal data recorded on physical media will be stored in locked filing cabinets only accessible by authorized personnel.

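### A baseline-constrained mixed model with the age stratum, in place of a difference in change with baseline significance tests, would give tighter effect estimates from the same data

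*Protocol article*

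**What the plan says.** **Model.** Section 2.7 (Statistical analysis) specifies "Linear Mixed Models with a random intercept fitted for subjects will be implemented using the lme4 package (60), to consider the repeated measures nature". Beyond the random intercept it names no model terms: no arm, visit, interaction, baseline or age term is stated as included or excluded.

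**Effect size.** The same section says: "Effect sizes will be calculated for the pairwise changes in primary outcome measures between the experimental conditions".

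**Visits.** Section 2.6.7 (Cognitive function) has two: "The benefit likelihood on cognitive function will be assessed pre- and post-intervention in a single sitting". Fatigue on the Short-Form 12 has three (Section 2.6.9): "pre-intervention, mid-intervention (end of Week 4) and post-intervention".

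**Baseline comparison.** Section 2.7 also says: "Group differences in baseline characteristics will be assessed with one-way ANOVA or Kruskal-Wallis test (pending normality of data".

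**Stratification.** Section 2.3 says: "All participants who give consent and fulfill the inclusion criteria will be stratified by age", with the cut shown only as 65 years with a plus/minus sign. Section 2.8 describes participant codes as "classified based on age stratification 65 years and younger or >66 years".

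**Use of the estimates.** Aim 2 is to provide initial effect estimates. The benefit-likelihood row of Table 1 and Section 2.6.7 also turn the direction of the cognitive effect sizes into a progression criterion.

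**The concern.** With two visits and complete data, a random-intercept model with arm, visit and their interaction reproduces the difference in mean change between arms. That estimator subtracts the whole of each man's baseline score, although only the fraction rho of a baseline deviation is expected to persist. The excess subtraction adds noise and pushes the estimate in the direction opposite to any chance baseline imbalance.

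At 19 per arm such imbalance is not small. The estimates affected serve aim 2, and their signs feed a go/no-go rule.

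Two neighbouring statements add to this. Significance tests of baseline differences between randomised arms test a null hypothesis that is true by design, so their p-values cannot show whether adjustment is needed. And the age classes do not cover every age, which matters if age is both the stratifier and a model term. Section 2.2 expects mainly older men, so participants aged 65 or 66 are likely.

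**Working it through.** **Inputs.** 19 men per arm (Section 2.4). Two visits for cognition (Section 2.6.7). Outcome in SD units with equal variance at both visits (assumption). Pre-post correlation rho: not in the article, so an assumption shown over a range. The article gives no standard error for a pairwise contrast, so there is no figure of its own to reproduce here.

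**Formulas for one pairwise contrast, n per arm.**
- Difference in change: Var = (2/n) × 2(1 − rho)
- Baseline-constrained: Var = (2/n) × (1 − rho²)
- Ratio: (1 − rho²) / [2(1 − rho)] = (1 + rho)/2, below 1 for every rho < 1

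**Example, rho = 0.5.** Change: sqrt(2/19 × 1.00) = 0.324. Constrained: sqrt(2/19 × 0.75) = 0.281. Reduction: 1 − sqrt(0.75) = 13%.

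| rho (assumed) | SE, change | SE, constrained | SE reduction | Change-score n per arm for the same precision, 19 × 2/(1 + rho) |
|---|---|---|---|---|
| 0.3 | 0.384 | 0.309 | 19% | 29.2 |
| 0.5 | 0.324 | 0.281 | 13% | 25.3 |
| 0.7 | 0.251 | 0.232 | 8% | 22.4 |
| 0.8 | 0.205 | 0.195 | 5% | 21.1 |
| 0.9 | 0.145 | 0.141 | 3% | 20.0 |

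**Simulation check** (both random-intercept models, 19 per arm, 150 data sets per rho). Mean model-based SEs agree with the formulas: 0.320 to 0.280 at rho 0.5, 0.252 to 0.233 at 0.7, 0.206 to 0.196 at 0.8. The empirical spread of the estimates also fell each time (0.314 to 0.305, 0.248 to 0.235, 0.196 to 0.184). With 150 runs each spread has a relative error of about 1/sqrt(2 × 149) = 6%, so the formulas are the better guide to size. They treat rho as known, so the realised gain is slightly smaller.

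**Carry-over of chance imbalance.** The SD of a pairwise baseline difference is sqrt(2/19) = 0.32 SD. Given an observed imbalance, the change estimate shifts by (1 − rho) times it, in the opposite direction: about 0.5 × 0.32 = 0.16 SD at rho 0.5 and 0.3 × 0.32 = 0.10 SD at rho 0.7 for a one-SD imbalance. The planning effect in Section 2.4 is d = 0.24.

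**Effect on the sign criterion, one outcome.** If the true effect were 0.24 SD and rho 0.5, the chance of a wrong-signed estimate is Φ(−0.24/0.324) = Φ(−0.74) = 23% for change and Φ(−0.24/0.281) = Φ(−0.85) = 20% for the constrained model.

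**What age adds.** Suppose the age stratum explains a share R² of outcome variance (assumed 5–10%). The correlation given age is r = (rho − R²)/(1 − R²) and the variance factor is (1 − R²)(1 − r²). At rho 0.5 and R² 0.10: r = 0.444, factor 0.722 against 0.750, SE reduction 1.9%. At rho 0.8 and R² 0.05: 0.3%.

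**Age classes side by side.** Section 2.3's plus/minus 65 does not place a man aged exactly 65. Section 2.8 places him in the younger class, but its upper class starts above 66, so a man aged 66 is in neither.

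**Limit.** The two-visit formulas do not apply to Short-Form 12 fatigue with its mid-point visit. The constrained model can be fitted there too, but its gain was not computed.

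**The case against.** The article lists no fixed effects. A reader might infer that the age stratum is left out of the model. The text does not support this: it is silent, and a term list is what an article commonly leaves to the full protocol or analysis plan. The difference-in-change reading is likewise an inference. A random-intercept model without an arm main effect is already baseline-constrained, and it too yields contrasts in change from a common baseline. The wording on pairwise changes favours the first reading but does not exclude the second.

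A reader might also infer that the change estimate is biased. It is not: over repeated randomisation both estimators are unbiased, and the shift shown above is conditional on the imbalance observed. Nor does leaving out age inflate the error of a change contrast much, since a stable age effect cancels within each man and allocation is already stratified on age.

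The gain is modest. At rho 0.7 the 95% half-width moves from 0.49 to 0.45 SD, still wide against d = 0.24. Primary outcomes are feasibility measures (Section 2.6.1), Section 2.6.2 reads mixed findings holistically with priority to safety and acceptability, and Section 2.7 already urges caution with hypothesis tests.

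Finally, one might attach a false-positive rate to the baseline tests, or say that they will steer covariate choice. The article gives neither their number nor their significance level, and does not say that they select covariates.

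All of this stands, and it limits the point to an improvement. It does not remove the stated baseline tests, the gap in the age classes, or the precision available at no cost.

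**Conclusion.** Upheld as a free improvement. On the natural reading of Section 2.7, the cognitive effect estimates are differences in change: valid, but with a standard error about 5% to 13% larger than need be for rho between 0.8 and 0.5, when expressed as the reduction that a baseline-constrained model gives. This rests on an assumed rho, equal variances at the two visits, 19 men per arm and two-visit outcomes. The second gain is that the estimate no longer carries chance baseline imbalance. The age term is there to match the randomisation, with little further precision to expect.

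Two textual points hold without any assumption on rho: the baseline tests are uninformative by design, and the age classes in Sections 2.3 and 2.8 do not agree or cover every age. Neither point, nor the choice of model, invalidates the analysis or bears on the feasibility outcomes other than the effect-size criterion in Table 1.

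**What to change.** 1. In Section 2.7, state a constrained longitudinal model: a common baseline mean in all arms, visit, arm-by-post-baseline visit, the age stratum used in randomisation as a fixed effect, and a random subject intercept. Section 2.3 withholds allocation until baseline testing is complete, so the common baseline mean holds by design.
2. Report adjusted arm differences with confidence intervals for cognition, fatigue and quality of life.
3. Replace the baseline ANOVA/Kruskal-Wallis tests with a descriptive table by arm.
4. Define the two age strata once, so that every age in completed years falls in exactly one, and use that definition in Sections 2.3 and 2.8. It should match the boundary actually used to build the allocation lists.

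The cost is a few sentences and one degree of freedom for age. Data, visits and software (lme4) stay the same.

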### Participants

2.2

The recruitment target is 76 men with prostate cancer over an ~18-month period. Participants will be recruited from the Australian Capital Territory (ACT) and surrounds utilizing the multidisciplinary team’s professional and clinical networks including public and private hospitals. The research team is highly connected to potential recruitment groups. The team includes a Medical Oncologist at The Canberra Hospital and the President of the ACT Prostate Cancer Support Group. The ICON Cancer Centre (co-located with the University of Canberra) will further support recruitment strategies. Outside of these direct routes of participant recruitment, the study will be advertised with flyers in cancer-related clinics, aged care settings and via traditional and social media outlets.

The annual incidence of prostate cancer in the ACT is approximately 260 new cases (35). The recruitment target requires a participation rate of 19.5% of the approximate 390 cases expected in the 18 months the study will be recruiting within.

Eligible participants must meet the following inclusion criteria:

Male >18 years old, diagnosed with prostate cancer currently receiving primary ADT for either metastatic or nonmetastatic hormone-sensitive prostate cancer.Received at least one dose of ADT within the last 6 months.Self-assessed reading and writing English proficiency.Able to provide written informed consent and expected life expectancy of more than 12 months.

Although eligibility is open to men aged ≥18 years to maximize inclusivity, the study population is expected to consist predominantly of older adults, as prostate cancer incidence and the use of androgen deprivation therapy are highest in this age group.

Based on known interactions with the primary outcome measures, participants will be excluded if (1) they have received chemotherapy or radiation within the last 3 months; (2) they are treated with steroids equivalent to more than 10 mg of prednisolone a day; (3) they have consumed opioid-based analgesics within the last 28 days; (4) they have a history of neurological injury/illness; or (5) they suffer from a concomitant major psychological illness (i.e., bipolar disorder or psychosis).

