### Sample size and power calculation

2.4

Determining sample sizes in pilot studies typically uses various methods to select samples that are representative of the population of interest. These methods have included less stringent justifications, often applying concepts related to a ‘rule of thumb.’ Sample size must ultimately provide sufficient representation of the population to assess feasibility and acceptability. However, it should also provide initial effect estimates to inform progression to larger trials. In line with recommendations for efficient and timely pilot studies (36), we have undertaken a modified power analysis utilizing an adjusted alpha (*α* = 0.25). This approach prioritizes the identification of preliminary effect signals that may warrant further investigation in a fully powered trial, while recognizing that any findings at this stage are exploratory and will be interpreted with appropriate caution.

As a result, we propose to recruit 77 participants, which will result in 19 per intervention arm in a 1:1:1:1 ratio. To inform this initial power analysis, we utilized a meta-analysis (28), comparing concurrent training to physical training in older adults. This power analysis was based on a four-arm study, with an effect size of *d* = 0.24, 80% power with *α* = 0.25.

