### Progression criteria

2.6.2

This pilot clinical trial will provide insights (e.g., feasibility, statistical power, effect estimates) which will guide the development of a larger-scale clinical trial that will aim to improve the cognitive and fatigue outcomes in men affected by prostate cancer receiving ADT. Clinical trial progression criterion as recommended (39), accounts for recruitment success, adherence, adverse events, subjective accounts of the intervention, and the likelihood of benefit. Table 1 provides an overview of the criterion and decision-making related to the progression to a larger trial—each of which are detailed below. As indicated in the progression criteria, further feasibility work may be required depending on the findings of the present study. Mixed findings will be interpreted holistically across criteria, with priority given to safety and acceptability to inform progression and protocol refinement.

**Table 1 tab1:** Suggested progression criteria for seeking funding for a larger trial.

Outcome measures	Not to progress to clinical trial	Potentially progress with revisions	Progress to clinical trial
Recruitment	Project recruits <50% sample size in designated time frame. Consider alternate designs/qualitative work to understand why.	Project recruits <100% sample size in designated time frame. Evaluate multi-site/locality implications for large trial. Consider qualitative work to understand best recruitment strategies/barriers.	Project recruits designated numbers in proposed timeframe. Consider locality/ies for larger trial based on power analysis.
Adherence	Adherence is <50%.	Adherence is 50–65%, consider factors to increase adherence.	Adherence is higher than 65%.
Adverse Events	Occurrence of any significant adverse events deemed to relate directly to the intervention.	Occurrence minor adverse events (e.g., increased fatigue) consider if protocol changes can be made.	No adverse events reported.
Subjective participant experience	Subjective accounts are overall negative.	Subjective accounts are neutral. Consider how participant experience could be managed to improve subjective outcomes.	Subjective accounts are overall favorable. (>50% positive descriptive data, supported qualitatively)

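### Section 2.7 reads each between-arm Cohen's d as small, moderate or large from the point estimate; at 19 per arm, with an assumed pre-post correlation of 0.5 to 0.8, a contrast with no true effect reaches the 'small' cut-off in about 33–54% of cases

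*Protocol article*

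**What the plan says.** Section 2.7 estimates intervention effects with linear mixed models that have a random intercept per participant. It then turns to standardised effects: "Effect sizes will be calculated for the pairwise changes in primary outcome measures between the experimental conditions". The denominator of d is described as "using the pooled standard deviation of the random effects to account for a Linear Mixed Model structure". The reading rule follows: "Effect sizes will be interpreted as small, moderate, and large based on cut-off points of 0.2, 0.5 and 0.8, respectively".

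The same section warns, when discussing hypothesis tests in pilot studies, that "the small sample sizes can result in imprecise estimates and are unlikely to reach statistical significance". Section 2.4 adds that findings at this stage are exploratory and will be read with caution.

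The estimates have a declared use. Section 2.4 wants the sample to yield initial effect estimates that inform progression, and section 2.6.2 says: "This pilot clinical trial will provide insights (e.g., feasibility, statistical power, effect estimates) which will guide the development of a larger-scale clinical trial". The benefit row of Table 1 refers to the direction of effects across most cognitive outcomes and does not mention the size labels.

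On numbers, section 2.4 states "we propose to recruit 77 participants, which will result in 19 per intervention arm in a 1:1:1:1 ratio".

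**The concern.** A size label on a point estimate is informative only if the estimate is precise relative to the gaps between the cut-offs. Those gaps are 0.2 (from zero to small) and 0.3 (small to moderate, and moderate to large). If the standard error of d is of that order, the label depends heavily on chance.

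Section 2.7 plays down significance tests and concedes imprecision, yet the one reading rule it fixes for d takes no account of that imprecision. The label could then be wrong in either direction. A null contrast may be written up as a small effect, or a true effect of the planned size may be passed over. Readers designing the larger trial would see the label before they saw how little supports it.

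**Working it through.** **Inputs from the article.** There are 19 participants per arm (section 2.4); 4 × 19 = 76, which matches section 2.2 ("The recruitment target is 76 men with prostate cancer over an ~18-month period"), although section 2.4 writes 77. The cut-offs are 0.2, 0.5 and 0.8 (section 2.7). Cognition is measured twice, before and after the intervention (section 2.6.7). The planning effect is d = 0.24 (section 2.4).

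**Assumed.** The pre-post correlation ρ is not given. I take 0.5 to 0.8 as the working range and show 0.3 and 0.9 as well. I scale d by the total SD and assume no dropout; losses would widen everything below.

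**The plan's own sample size.** The stated inputs are "with an effect size of *d* = 0.24, 80% power with *α* = 0.25". Read as a plain two-arm comparison, n per arm = 2(z₁₋α/₂ + z₀.₈)²/d² = 2(1.150 + 0.842)²/0.24² = 138 two-sided. The one-sided figure is 2(0.674 + 0.842)²/0.24² = 80. Neither gives 19. That is a separate matter: the check below needs only 19 per arm and the cut-offs.

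**Standard error.** For a difference between two arms in mean change, in total-SD units:

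SE(d) = √[(2/19) × 2(1 − ρ)] = √[4(1 − ρ)/19]

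At ρ = 0.5 this is √(2/19) = 0.324. At ρ = 0.8 it is √(0.8/19) = 0.205.

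**No true effect.** The chance that d is at least c in absolute value is 2[1 − Φ(c/SE)].

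| ρ | SE of d | at least 0.2, either direction | at least 0.5, either direction | 95% half-width (1.96 × SE) |
|---|---|---|---|---|
| 0.3 | 0.384 | 60% | 19% | 0.75 |
| 0.5 | 0.324 | 54% | 12% | 0.64 |
| 0.7 | 0.251 | 43% | 5% | 0.49 |
| 0.8 | 0.205 | 33% | 1.5% | 0.40 |
| 0.9 | 0.145 | 17% | 0.1% | 0.28 |

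In favour of one named arm, the 0.2 figure halves to 27% at ρ = 0.5 and 16% at ρ = 0.8. A simulation of 20,000 four-arm trials per correlation, with the SD estimated from the data, gave 54.1% at ρ = 0.5 and 33.5% at ρ = 0.8. In the same simulation, at least one of the three contrasts of concurrent training with the other arms reached 0.2 in 87% and 65% of null trials, per outcome.

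**Planned effect true (d = 0.24).**
- Estimate below 0.2: Φ(−0.04/SE) = 45% at ρ = 0.5 and 42% at ρ = 0.8.
- Estimate negative: Φ(−0.24/SE) = 23% and 12%.
- Estimate at least 0.5: 1 − Φ(0.26/SE) = 21% and 10%.
- The 95% interval around an observed 0.24 is −0.40 to 0.88, or −0.16 to 0.64.

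**Sensitivity to the method.** If the SD of the random effects means the random-intercept SD alone, SE = √[4(1 − ρ)/(19ρ)] and the null range for 0.2 becomes 66% to 38%. If the contrast were adjusted for baseline, SE = √[2(1 − ρ²)/19] and it becomes 48% to 30%.

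**The case against.** The strongest reply is that the labels decide nothing. Table 1 judges benefit by the sign and consistency of effects, and the definition of potential harm in section 2.6.7 does the same. That stands: a reader might infer that a chance 'small' or 'moderate' would trigger progression, and the article does not support this.

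A reader might also infer that the next trial will be sized on the observed d. Section 2.6.2 says only that power and effect estimates will guide its development, so mis-sizing is a risk and not a stated step.

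A third reply is that this is a condensed article, and intervals may well be specified in a fuller document. That also stands. The absence of an interval here is not an error in itself; the point concerns a reading rule that the article does state.

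The protocol also urges caution twice. This is true and to its credit. But one caution is attached to hypothesis tests and the other is general, and neither changes how d is to be read.

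Finally, the size of the problem should not be overdrawn. The correlation is assumed, and the 33–54% counts both directions. A false 'moderate' or larger is much rarer, at 12% to 1.5% per contrast over the working range. Section 2.7 also ties effect sizes to primary outcome measures. The cognitive measures come in through the benefit criterion, whereas section 2.6.8 lists fatigue and quality of life as secondary, so the labelling sentence may not reach every Aim 2 outcome. Benchmarks of this kind are conventional descriptions and do not claim that an effect exists.

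**Conclusion.** The point holds as a minor one. The stated rule attaches a size label to an estimate whose standard error, about 0.32 to 0.21, is of the same order as the gaps between the cut-offs. Under no true effect, roughly a third to a half of contrasts would reach at least 'small' in one direction or the other.

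This rests on 19 completers per arm, d on the total-SD scale and an assumed pre-post correlation of 0.5 to 0.8. The direction of the conclusion does not depend on the SD chosen, but its size does depend on the correlation. At 0.9 the rule would mislabel about one null contrast in six. The consequence is confined to how effects are described and handed on to the planning of the larger trial.

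**What to change.** In section 2.7, replace the labelling sentence with:

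> Each between-arm effect from the mixed model will be reported on the raw scale and as d with its 95% confidence interval; the size of an effect will be described from the range of the interval, and no small/moderate/large label will be given on the point estimate alone.

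In section 2.6.2, add that the observed d will be carried into planning of the larger trial only together with its interval.

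The cost is two sentences and an interval column in the results tables, with no new data. The drawback is that the reported results will look less definite, which at this sample size is an accurate picture.
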